### Trial design {8}

This protocol refers to a randomized superiority trial. This is a prospective, open, single-center, positive-controlled study, with two parallel groups, assigned as a split-mouth model, whereupon each side of the mouth will be allocated as an independent unit and each patient will receive both treatments, test and control.

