#### Preparation and installation of the autogenous bone graft and Plenum^®^ Oss 3D_β_ fit

The intra- and extra-oral asepsis will be performed with 0.12% and 2% chlorhexidine digluconate. Next, the local anesthesia will be applied with Articaine 4% 1:100.000 (Nova DFL, Brazil), followed by a linear incision over the alveolar crest and two vertical incisions. Next, the mucoperiosteal flap will be detached, and the autogenous bone graft collection will be started. A linear incision will also be made in the donor site, followed by a mucoperiosteal flap detachment and a mandible branch exposure. Trunk-conical drills and discs mounted in a straight handpiece will be used for osteotomy. After the graft removal, it will incubate in saline solution while the receptor site is prepared. Grooves will be performed in the receptor site to stimulate the vascularization, and the autogenous bone graft will be fixed in the anterior region of the maxilla by fixing screws. On the opposite side of the maxilla (test group), grooves will also be performed, and the 3D printed block will also be fixed by fixing screws. Then, a resorbable polydioxanone membrane, Plenum^®^ Guide (Plenum, Jundiaí, São Paulo, Brazil) will be used over 3 to 4 mm of the bone grafts, and the suture will be performed with Nylon 5.0 (Ethicon^®^, Jonhson & Jonhson, New Brunswick, Nova Jersey, EUA). All surgical procedures will be performed by the same professional.

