## Assignment of interventions: allocation

### Sequence generation {16a}

The treatments will be randomized using 20 binary sets (0- control treatment: autogenous graft and 1- test treatment: Plenum^®^ Oss 3D_β_ fit). The sets, 1 to 20, will correspond to each patient according to the enrolment order. The binaries numbers 0 and 1 will be randomized, corresponding to the treatment that will be applied. From left to right, the first number will define the treatment of the right side of the maxilla, and the second number will determine the treatment which will be applied on the left side.

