## Statistical methods

### Statistical methods for primary and secondary outcomes {20a}

Data from this study will be analyzed for their distribution by the Shapiro-Wilk normality test. If the data are distributed according to normality, parametric tests will be used for the inferential analysis of the data. The comparison between groups in each experimental period will be performed using the unpaired *t*-test. The longitudinal evaluation of these data within each group will be evaluated using the ANOVA test for repeated samples complemented by the Tukey test. If the data are not distributed according to normality and the qualitative parameters, they will be analyzed inferentially using non-parametric statistical tests. The comparison between groups in each experimental period will be performed using the Mann-Whitney test. The longitudinal evaluation of these data within each group will be evaluated using the Friedman test complemented by the Dunn test. The BioStat software version 5.3 will be used to perform the statistical analysis of this project.

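### Right/left placement is the only thing randomised, but no side balance is stated and the planned test ignores both patient and side; a balanced list and a within-patient analysis with a side term would be a cheap, minor improvement

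*Protocol article*

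**What the plan says.** The Trial design section states that "each patient will receive both treatments, test and control", so treatment is balanced within every patient. What remains to be randomised is the side. Under Sequence generation, "The treatments will be randomized using 20 binary sets", one set per patient in enrolment order. Within a set "The binaries numbers 0 and 1 will be randomized, corresponding to the treatment that will be applied", and "the first number will define the treatment of the right side of the maxilla", with the second number deciding the left. Nothing is said about how often test should fall on the right across the 20 sets. The Concealment mechanism section adds only the software.

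The surgical section states that "All surgical procedures will be performed by the same professional". For the analysis, the Statistical methods section fixes "The comparison between groups in each experimental period will be performed using the unpaired *t*-test", or, if the data are not normal, "The comparison between groups in each experimental period will be performed using the Mann-Whitney test". Neither test has a term for patient or side.

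**The concern.** Side plays the part here that period plays in a two-period crossover. With a single operator, a right-left difference arising from access or handedness would point the same way in every patient and would not average out over surgeons. Two things follow if such a difference exists.

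- If test happens to fall on the right more often than on the left, part of the side difference is counted as a graft difference in the list actually drawn.
- Even in a 10:10 list, leaving side out of the model puts the side difference into the error term of a 20-patient comparison.

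At stake is precision in a small trial and, for the unpaired test, a modest departure from the nominal error rate.

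**Working it through.** **Inputs.** From the Sample size section: difference 11.90 percentage points of volumetric reduction, SD 12.09, power 0.80, α 0.05, 20 participants with two grafts each. Assumptions of this check: two-sided test; 12.09 is the per-graft SD; within-patient correlation ρ of 0 or 0.5; right-left difference s of 0, 3, 6 or 10 points, the same in all patients. At ρ = 0.5 the SD of the within-patient difference is 12.09 × √(2 × 0.5) = 12.09. That case therefore also covers, for the paired analysis, a reading of 12.09 as the SD of differences.

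**The plan's own figure.** A two-sample t-test with 11.90 and 12.09 needs 18 per group (17 by normal approximation). A paired test with 12.09 as the SD of differences needs 11. The stated 20 is near the two-sample result, and 20 per group gives 86% power.

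**Side imbalance.** If the 20 sets are ordered independently, the number k with test on the right is Binomial(20, 0.5):

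- exactly 10:10: 0.176
- 13:7 or worse: 0.263
- 14:6 or worse: 0.115

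Test minus control is shifted by +s when test is on the right and by −s when it is on the left, so the shift in the mean is s(2k − 20)/20. At 13:7 it is 0.3s and at 14:6 it is 0.4s. With s = 6, the 14:6 shift is 2.4 points, or 2.4/11.90 = 20% of the target difference. The average absolute shift is 0.176s. Over all lists the shift averages zero.

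**Variance.** Under independent ordering, Var(graft difference) = [2 × 12.09² × (1 − ρ) + s²]/20. For ρ = 0 and s = 6: (292.3 + 36)/20 = 16.4, SE 4.05, against 3.82 at s = 0.

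**Power and type I error** at a true difference of 11.90. The paired figures are noncentral t; the planned unpaired test was simulated, with at least 40,000 runs per cell.

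| ρ | s | SE | Paired, no side | Planned unpaired | Type I, unpaired |
|---|---|---|---|---|---|
| 0 | 0 | 3.82 | 84% | 86% | 0.05 |
| 0 | 3 | 3.88 | 83% | 85% | 0.05 |
| 0 | 6 | 4.05 | 80% | 83% | 0.06 |
| 0 | 10 | 4.43 | 72% | 78% | 0.07 |
| 0.5 | 0 | 2.70 | 99% | 93% | 0.01 |
| 0.5 | 3 | 2.79 | 98% | 92% | 0.01 |
| 0.5 | 6 | 3.02 | 96% | 90% | 0.01 |
| 0.5 | 10 | 3.51 | 90% | 84% | 0.02 |

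The paired test without side keeps its type I error at about 0.05 throughout. At ρ = 0 and larger s, part of the unpaired test's higher power comes from its inflated type I error.

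**With a 10:10 list and a side term** (18 degrees of freedom), s drops out. The SE is 3.82 or 2.70, and power is 84% (ρ = 0) or 99% (ρ = 0.5) for every s.

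**Which part of the change does the work.** A side term with an unbalanced list gives about 81-82% at ρ = 0, so balance itself is worth about 2 points. Balance without the term is not enough: at s = 12 and ρ = 0, a paired test then has type I error 0.019 and power 70%. At ρ = 0.5 and s = 0, the move from 93% to 99% is due to pairing alone.

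**The case against.** The case against has several parts.

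- **Lack of balance is read from silence.** The article neither states a ten-ten split nor excludes one, and list restrictions and model terms are often left to fuller documents. This stands as a limit: the binomial figures hold only if sets are ordered independently. It does not dispose of the point, because the article does fix the between-group tests, and those contain neither patient nor side.
- **The allocation is not biased.** A reader might infer from the 0.4s shift that the randomisation is faulty or the trial biased. The documents do not support that. Randomising side within each patient is valid, the estimate is unbiased over lists, and a paired test already counts the imbalance as random error.
- **The size is assumed.** A reader might also infer a serious loss of power. The protocol gives no right-left difference, and at its own target of 11.90 the planned test loses about 3 points of power at s = 6 and stays above 80%. This objection stands.
- **The outcome limits the mechanism.** The Volumetric analysis section measures resorption from a post-operative scan to eight months, so a side difference in the volume placed is largely absorbed in the reference. To matter, s must act on later percentage resorption. This also stands.
- **Pairing is the larger issue.** At small s, most of what can be gained comes from replacing the unpaired test, and then only if the two sides of a mouth are correlated. This is conceded.

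**Conclusion.** The point holds as a minor refinement. The protocol states no side balance and plans a comparison that ignores patient and side. Nothing in it is invalid, and no stated figure is wrong. If a right-left difference exists, it adds about s²/20 to the variance and shifts the estimate by 0.4s in a 14:6 list. At 11.90 and 12.09 the effect is negligible at s = 3 and small at s = 6. It becomes material only when s approaches the treatment difference: at s = 10 the planned test has 78% power (ρ = 0) or 84% (ρ = 0.5), against a constant 84% or 99% after the change. At ρ = 0 the planned test's type I error would be about 0.06-0.07 for s = 6-10; at ρ = 0.5 it would be about 0.01-0.02, which is conservative. All of this rests on the assumed s and ρ, on independent ordering of sets, and on 12.09 being the per-graft SD.

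**What to change.** Generate the list as ten 0-1 sets and ten 1-0 sets in random order. Replace the unpaired comparison with an analysis of within-patient differences that includes a right/left term, as in a 2×2 crossover: the graft effect is the average of the two mean differences, one from patients with test on the right and one from those with test on the left. Both parts are needed, since balance without the term leaves s in the error. Because dropouts are replaced until 20 are complete, also state which set a replacement receives, so that the balance survives.

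The Trial status section says recruitment had yet to start, so the list costs nothing to change at that stage, and the analysis needs one added term. The side term costs one degree of freedom, about 0.2 points of power if s = 0. If the two sides are uncorrelated and s = 0, moving from the unpaired to the paired analysis costs about 2 points (86% to 84%). The last assignments become slightly more predictable, but only as to side, because every patient receives both grafts.

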### Concealment mechanism {16b}

Randomization of treatments will be performed using the ResearchRandomizer software (https://www.randomizer.org/).

### Implementation {16c}

The trial sponsor and the Principal investigator team will generate randomization with the allocation sequence.

## Assignment of interventions: blinding

### Who will be blinded {17a}

Not applicable; this is an open trial.

### Procedure for unblinding if needed {17b***}***

Not applicable; this is an open trial.

## Data collection and management

### Plans for assessment and collection of outcomes {18a}

For security, CT scans will be saved on the M3 Health’s server, which already has a security protocol. The biopsies analysis will be performed with positive controls for the antibody reactions.

Data management will follow the same procedures for verification, validation, and security of electronic systems used by the sponsoring company, M3 Health.

### Plans to promote participant retention and complete follow-up {18b}

Data from participants which have already been collected will be used in the analysis referring to the completed steps, even if they do not conduct the clinical investigation.

### Data management {19}

Data will be maintained at Electronic File Management System (SharePoint platform, Microsoft 365) and organized by the study sponsor. The hardcopy source documents will be stored at M3 Health in an appropriate room with controlled access. Patients’ identity will be determined by a letter/number code composed of the first and last letter of the name, the first and last letter of the last name, and the birth year. The CRFs will be transcribed to electronic forms, after the patient’s visit by the Ph.D. students, as a backup measure and also to report adverse events to the sponsor. These forms will be prepared by the sponsor, and after they are filled in, they will be saved, in a pdf file, on the company's server.

### Confidentiality {27}

According to the current legislation regarding General Law of Data Protection (LGPD), number: 13.709/2018.

### Plans for collection, laboratory evaluation, and storage of biological specimens for genetic or molecular analysis in this trial/future use {33}

Not applicable; the study will not collect biological specimens for genetics or molecular analyses.

## Statistical methods

### Statistical methods for primary and secondary outcomes {20a}

Data from this study will be analyzed for their distribution by the Shapiro-Wilk normality test. If the data are distributed according to normality, parametric tests will be used for the inferential analysis of the data. The comparison between groups in each experimental period will be performed using the unpaired *t*-test. The longitudinal evaluation of these data within each group will be evaluated using the ANOVA test for repeated samples complemented by the Tukey test. If the data are not distributed according to normality and the qualitative parameters, they will be analyzed inferentially using non-parametric statistical tests. The comparison between groups in each experimental period will be performed using the Mann-Whitney test. The longitudinal evaluation of these data within each group will be evaluated using the Friedman test complemented by the Dunn test. The BioStat software version 5.3 will be used to perform the statistical analysis of this project.

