### Sample size {14}

Sample calculations were performed based on tomographic bone formation data from the study, which evaluated the volumetric stability of autogenous and allogeneic corticomedullary block grafts used for volume increase associated with edentulous alveolar ridges [19]. This choice was due to the lack of studies comparing β-tricalcium phosphate blocks and autogenous bone and the similarity of the methodology for evaluating the stability of block grafts. As a result, it was verified that the minimum difference between the means of treatments concerning the percentage of volumetric reduction of the graft was 11.90, with a standard deviation of 12.09. Therefore, considering a study power (1-β) of 0.8 and an *α* power of 0.05, a minimum sample of 20 participants was determined, each of whom will receive two grafts, one synthetic in a personalized block and another in an autogenous block. To maintain the power of the study, the sample size should be maintained, thus if any participant dropout or is discontinued before the analysis of the primary outcome, a new participant will be recruited instead, until complete 20 participants.

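### A normality pre-test decides whether the primary comparison tests means or ranks, so the primary test and its target are not fixed in advance

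*Protocol article*

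**What the plan says.** The section on statistical methods for primary and secondary outcomes {20a} sets one rule for all outcomes. It begins with a pre-test: "Data from this study will be analyzed for their distribution by the Shapiro-Wilk normality test". The branch follows: "If the data are distributed according to normality, parametric tests will be used for the inferential analysis of the data".

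- If normality is accepted: "The comparison between groups in each experimental period will be performed using the unpaired *t*-test".
- If it is not: "The comparison between groups in each experimental period will be performed using the Mann-Whitney test".

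Two other sections bear on this. Sample size {14} plans on means: "the minimum difference between the means of treatments concerning the percentage of volumetric reduction of the graft was 11.90", with a standard deviation of 12.09. Trial design {8} makes the data paired, since "each patient will receive both treatments, test and control", and states the aim: "This protocol refers to a randomized superiority trial".

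The statistical section mentions neither within-patient differences nor residuals. It gives no significance level for the pre-test and does not say which set of values is tested.

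**The concern.** The two branches answer different questions. The t-test asks whether mean volume reduction differs between grafts, which is the quantity the trial was sized on. Mann-Whitney asks whether values on one graft tend to exceed those on the other, and it responds to differences in spread and shape as well as location. Under the rule, which question the trial answers depends on how the observed sample happens to look.

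The pre-test also seems aimed at the wrong distribution. With both grafts in each patient, the assumption behind a sensible mean comparison is that the within-patient difference is roughly normal. Raw values may be skewed only because patients differ from one another, and that shared part cancels in the difference. A pre-test on raw values can then send the analysis to ranks when nothing is wrong with the mean analysis.

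At stake is whether the superiority claim refers to a quantity fixed in advance.

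**Working it through.** **Inputs from the protocol article.** Difference in means 11.90, SD 12.09, power 0.80, alpha 0.05, 20 participants with one graft of each kind (Sample size {14}); both treatments in each patient (Trial design {8}).

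**Assumptions, because the article is silent.** Two-sided testing; 12.09 read as the SD per site; Shapiro-Wilk at 0.05, once per graft, on raw values; Mann-Whitney if either graft fails; within-patient correlation 0 to 0.7; skewed shapes as named below.

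**1. The plan's own figure.** For two independent means by the normal approximation, n per graft = 2 × (1.960 + 0.842)² × (12.09 / 11.90)² = 2 × 7.85 × 1.032 = 16.2, so 17. The t-based version gives 17.2, so 18. Dividing 17.2 by 0.864, the minimum relative efficiency of Mann-Whitney, gives 19.9, so 20. The stated 20 is therefore reachable from a mean-difference calculation, though the article does not say which route was taken.

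**2. Switching by chance.** With exactly normal data and two independent pre-tests, P(at least one fails) = 1 − 0.95² = 9.75%. Simulation with 20 pairs and 6,000 runs gives 9% to 10% at every correlation from 0 to 0.7.

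**3. Raw values against differences.** Patient effect skewed (gamma, shape 1.5), site errors normal, so the differences are exactly normal:

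| Correlation | Raw values fail in at least one graft | Differences fail |
|---|---|---|
| 0.5 | about 22% | about 5% |
| 0.7 | about 37% | about 5% |

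With exponential or lognormal patient effects the raw failures are 26% to 30% at correlation 0.5 and 45% to 46% at 0.7; the differences again fail in about 5%.

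**4. Type I error, grafts of like shape.** The two-stage rule stays within about 0.006 of the fixed unpaired t-test in every null scenario run (for example 0.051 against 0.050 with normal data at correlation 0). Ignoring the pairing does far more: with normal data, null rejection falls to about 0.025, 0.009 and 0.001 at correlations 0.3, 0.5 and 0.7, for the rule and the fixed unpaired t-test alike.

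**5. Type I error, grafts differing in both spread and skewness.** Equal means, one graft normal with SD 6, the other gamma or exponential with SD 12 (invented values; the article gives one SD). The rule rejects in about 12% to 16% at correlation 0, falling to about 6% to 8% at 0.7. At correlation 0 a Mann-Whitney test fixed in advance gives practically the same rates (12.0% and 16.1%, against 11.8% and 16.2% for the rule in the same runs), and the fixed t-test about 6% to 7%. With one graft skewed but equal SDs, the rule is at only 6.6%.

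**6. The proposed replacement.** For a paired t-test, SD of the difference = 12.09 × √(2(1 − ρ)). At ρ = 0 this is 17.10, so the noncentrality is 11.90 / 17.10 × √20 = 3.11 and power is 0.84. At ρ = 0.3, 0.5 and 0.7, power is 0.94, 0.99 and above 0.99. In the like-shape scenarios its type I error was 0.042 to 0.054. In the mismatched scenario at correlation 0 it was about 6%.

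**The case against.** The best defence is that the rule is itself prespecified. Both branches are written down, and the branch depends on a distribution test, not on the treatment effect. That stands: a reader might infer that the test is picked once the results are known, and the text does not support this.

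Second, the unit and level of the pre-test are operational details that a condensed article may leave to the full protocol or analysis plan. That also stands, so their absence is no finding, and the reading on raw values remains an inference. It is the natural one, because the text speaks of data and follows with two-sample tests. The switch itself is stated outright, whatever the unit.

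Third, the practical effect may be small. With normal data and a true difference of 6 to 11.9, the rule and a fixed t-test reach different verdicts in only 0.3% to 1.5% of trials. A reader might also infer that the rule substantially inflates false superiority claims. The documents do not support that: inflation appears only under an assumed mismatch in both spread and skewness, is largest at zero correlation, and comes from Mann-Whitney reacting to shape, not from pre-testing. Nor should one count a pre-test for every scan. The Volumetric analysis section compares the scan after grafting with the scan at eight months, which gives one value per graft for the primary endpoint.

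Finally, the unpaired tests are the larger error in the same section. True, but making both branches paired would leave the switch between means and ranks in place.

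**Conclusion.** The concern holds as one of an unfixed primary test and target. The article sizes the trial on a mean difference, then lets the trial's own data decide whether that difference is tested at all. Under the assumed pre-test (one per graft, raw values, level 0.05, n=20), the switch happens by chance in about 10% of trials with normal data. It happens in about 22% to 37% when patients vary in a skewed way (gamma, shape 1.5; correlation 0.5 to 0.7), although the differences are normal and fail only about 5% of the time.

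Material type I inflation is not established. These rates depend on assumed shapes, correlations and pre-test settings; that the rule switches between two targets depends on none of them.

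**What to change.** For the primary volume endpoint, remove the normality gate and name one analysis that applies whatever the distribution:

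- **Primary:** the mean within-patient difference in percentage volume reduction between the post-graft scan (T2, one week) and the eight-month scan (T3), by paired t-test with a 95% confidence interval. Give the times in words, since the participant timeline labels T2 and T3 differently from the Tomography section.
- **Sensitivity:** Wilcoxon signed-rank on the same differences, stated not to decide the conclusion.
- **Normality:** if examined, on the within-patient differences and as description only.

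Make this edit together with replacing the unpaired tests; neither correction removes the other fault. Under the planning values 20 participants remain enough (power at least 0.84 for correlations of 0 and above). The cost is wording, plus slightly less power than a rank test if the differences turn out heavy-tailed. If the grafts differ strongly in spread and skewness, the paired t-test may still run a little above its nominal level.

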### Methods for additional analyses (e.g., subgroup analyses) {20b}

Not applicable; all the analyses are already described in the study protocol.

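### The split-mouth trial pairs both grafts within each patient, but the protocol compares them with independent-sample tests, which hold their nominal level only if the within-patient correlation is zero

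*Protocol article*

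**What the plan says.** All references are to the protocol article.

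- Trial design {8} describes a split-mouth superiority trial in which "each patient will receive both treatments, test and control". The same sentence describes the groups as parallel and says that "each side of the mouth will be allocated as an independent unit".
- Sequence generation {16a} randomises within the patient: of the two binary digits, "the first number will define the treatment of the right side of the maxilla, and the second number will determine the treatment" for the left.
- Sample size {14} counts 20 participants with two grafts each. It plans on a treatment difference where "the percentage of volumetric reduction of the graft was 11.90, with a standard deviation of 12.09".
- Statistical methods {20a} covers primary and secondary outcomes. For normally distributed data: "The comparison between groups in each experimental period will be performed using the unpaired" t-test. Otherwise: "The comparison between groups in each experimental period will be performed using the Mann-Whitney test".
- The repeated-measures ANOVA and Friedman tests in {20a} are assigned to change over time within one graft group. They do not address the contrast between grafts.
- Methods for additional analyses {20b} adds that "all the analyses are already described in the study protocol".

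**The concern.** The two grafts in one mouth share the patient's healing, bone quality, hygiene and surgeon. The natural contrast is test minus control within the patient, and a split-mouth design is chosen to remove between-patient variation from that contrast. The unpaired t-test and the Mann-Whitney test treat the 40 grafts as 40 unrelated observations, which puts that variation back into the error term.

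The direction of the error depends on the correlation between sides. If it is positive, p-values are too large, intervals too wide and real differences easier to miss. If it is negative, the test rejects too often. The same tests govern the secondary between-graft comparisons (histomorphometry, immunohistochemical markers, implant stability, operative time), for which the article gives no power calculation.

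This is not a detail left to an analysis plan that is not shown. The article names the tests, and an analysis plan that followed it would repeat the mismatch.

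**Working it through.** **Inputs.** From Sample size {14}: n = 20 participants with two grafts each, difference 11.90, SD 12.09, power 0.80, alpha 0.05 (two-sided assumed). Not in the document: the within-patient correlation ρ (assumed range -0.2 to 0.7), and whether 12.09 is the SD of a single graft or of the within-patient difference (read as per-graft below). A difference of 8 is also an assumption, used to show a smaller effect.

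**The plan's own figure (20).** The formula used is not stated, so several were tried:
- Two-sample t-test, 11.90/12.09: 17.2, so 18 per group.
- The same divided by 0.864, the minimum efficiency of the Mann-Whitney test: 17.2/0.864 = 19.9, so 20.
- Paired t-test, 12.09 per graft, ρ = 0: 19 pairs.
- Paired t-test, 12.09 as the SD of differences: 10.2, so 11 pairs.

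The stated 20 is close to an independent-samples calculation, or to a paired one with zero correlation. The text does not settle which was meant.

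**Standard errors.**
- Assumed by the unpaired test: 12.09 × √(2/20) = 3.82, whatever ρ is.
- True value for the paired design: 12.09 × √(2(1-ρ)) / √20. This gives 4.19 (ρ = -0.2), 3.82 (0), 3.20 (0.3), 2.70 (0.5) and 2.09 (0.7).

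The two agree only at ρ = 0.

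**Interval width, unpaired to paired.** Ratio = t(0.975; 38) / [t(0.975; 19) × √(1-ρ)] = 2.024 / [2.093 × √(1-ρ)]. At ρ = 0.5: 2.024 / (2.093 × 0.707) = 1.37.

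**Type I error and power.** Simulated with 20 bivariate-normal pairs at two-sided 0.05, unpaired t (38 df) against paired t (19 df). Separate runs of 60,000 and 100,000 trials agree to about 0.1 percentage point on the type I error.

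| ρ | Type I error, unpaired | Width ratio | Power at 11.90, unpaired / paired | Power at 8 (assumed), unpaired / paired |
|---|---|---|---|---|
| -0.2 | 7.3% | 0.88 | 0.84 / 0.77 | 0.53 / 0.44 |
| 0 | 5.0% | 0.97 | 0.86 / 0.84 | 0.53 / 0.51 |
| 0.3 | 2.0% | 1.16 | 0.90 / 0.94 | 0.54 / 0.66 |
| 0.5 | 0.7% | 1.37 | 0.93 / 0.99 | 0.55 / 0.80 |
| 0.7 | 0.1% | 1.77 | 0.96 / >0.99 | 0.56 / 0.95 |

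The paired t-test stays between 4.8% and 5.1% throughout. The Mann-Whitney test shows the same pattern as the unpaired t-test: 7.1%, 4.9%, 2.2%, 0.9% and 0.1% in the order of the rows.

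**The case against.** The strongest reply is that little harm follows for the primary comparison. At the planned 11.90 the unpaired test exceeds 80% power at every correlation shown. With positive correlation, the plausible case for two sides of one mouth, it is conservative and would not manufacture a superiority claim. This stands, and it limits what can be said.

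Four stronger readings are tempting but not supported:

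- *Every between-graft p-value and interval is wrong.* The error vanishes at ρ = 0 and its size will differ between outcomes. The document gives no correlation for any of them. It also plans no confidence intervals by name, so the width figures apply only to intervals that someone derives from these tests.
- *The trial will falsely declare superiority.* Inflation needs a negative correlation, and nothing in the document suggests one.
- *The primary analysis is underpowered.* It is not, on the plan's own difference and SD. The contrast of 0.55 with 0.80 belongs to an assumed difference of 8, which is not in the document.
- *The Shapiro-Wilk step is part of the same error.* The text does not say which quantity is tested. Whether to choose a test by a normality check at all is a separate question and partly a matter of preference.

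What the reply does not do is justify the choice. A test whose actual level may lie anywhere from about 0.1% to 7.3%, depending on an unknown, is not the 5% test that the plan announces. It also discards the advantage for which both sides of each patient are operated on.

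**Conclusion.** The stated tests do not match the stated design. Within-patient randomisation produces 20 pairs, the article prescribes independent-sample tests for every between-graft comparison, and no other section corrects this.

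The consequence is a miscalibrated level whenever the correlation is not zero. With positive correlation there is also lost power: 4 to 6 percentage points at the planned 11.90 (ρ = 0.3 and 0.5), and 12 to 25 points at an assumed difference of 8. It therefore matters mainly for effects smaller than planned and for the secondary outcomes. These figures assume bivariate-normal data, equal SDs of 12.09 per graft, complete pairs and two-sided testing.

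The correction should still be made. The error is explicit, it governs the confirmatory comparison, and Trial status indicates that recruitment had not begun.

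**What to change.** **Statistical methods {20a}.** Replace the unpaired t-test by the paired t-test on the within-patient difference (test minus control), reported with its 95% CI. Replace the Mann-Whitney test by the Wilcoxon signed-rank test for ordinal or clearly non-normal outcomes. If normality is checked, check it on the differences.

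A mixed model with graft, side and a random patient effect is an alternative. It is not identical to the paired t-test, because the side term changes the model and the error degrees of freedom. It can, however, use patients with data on one side only. That may be needed for the mini-implant measurements, since mini-implants are placed only where there is ample bone.

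**Trial design {8}.** Remove the description of the groups as parallel and of the sides as independent units. State that the patient is the block and that the sides are randomised within it.

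**Sample size {14}.** State whether 12.09 is a per-graft SD or the SD of differences, and which correlation was assumed.

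**Cost.** Wording in three sections and a protocol amendment notice to the regulator under {25}, with no new patients, visits or data. If the correlation is zero or negative, the paired test has somewhat less power at 11.90: 0.84 against 0.86 at ρ = 0, and 0.77 against 0.84 at ρ = -0.2. In the latter case the unpaired figure comes with a type I error above 5%.
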